##### Inflammation

Systemic inflammation is a marker of IBD disease activity. Hence, only a sub-group of participants (i.e. those with IBD) will have their blood taken. Inflammation will be measured by C-reactive protein, white cell count, neutrophil count, platelet count and albumin. As markers of inflammation, these laboratory results will indicate any changes in inflammatory response in the participant.

#### Participant timeline

Figure 1 illustrates the process of enrolling participants in the study and timing of intervention and measurements. Figure 2 displays the SPIRIT figure of enrolments, interventions and assessments.

**Fig. 1 Fig1:**
[figure not shown]
Participant Flowchart

**Fig. 2 Fig2:**
[figure not shown]
SPIRIT figure of enrolments, interventions and assessments. Asterisk denotes that t1–t12 represents the 12 weeks of a physical activity intervention

#### Sample size

It is inappropriate to base feasibility study sample sizes on measures of intervention effect, which is the purpose of the full-scale trial. Although how many participants are required in a feasibility study remains equivocal, suggestions range from 10 to 75 [32]. We aim to recruit 30 participants across three sites which should provide a sample of participants with different demographic and clinical characteristics that will improve our confidence in the conclusions we draw from this feasibility study.

#### Recruitment

Three recruitment methods will be used and the number of patients recruited by each method will be compared:

##### Prospective

A stoma/colorectal nurse specialist will discuss the study with eligible patients and, if they are interested, will pass their contact details on to a member of the research team. Verbal consent will be obtained. A researcher will then contact the patient to organise a face-to-face meeting where they will explain the study in further detail and take informed consent from the participant.

##### Retrospective

A list of potentially eligible patients will be put together by the clinical team. This list will be anonymised by removing name and contact details so that a member of the research team can re-assess patients for eligibility. The clinical team will send a letter of invitation to those that are eligible. Those that are interested will get in touch with the research team so that eligibility can be confirmed and to explain the study in more detail and take informed consent.

##### Social media

Recruitment via social media will also be used to maximise recruitment numbers. An advertisement about the study will be disseminated by members of the Patient Advisory Group and by relevant stoma charities on both Facebook and Twitter. Contact details of the research team will be provided, along with brief eligibility criteria. This will allow anyone who is interested in taking part to see if they will be eligible and to contact the research team directly.

#### Data collection

Data to evaluate the main outcomes of the feasibility study will be collected as follows: to collect data to assess intervention implementation, PA instructors will keep a paper record of each PA consultation with each participant; to collect data to assess intervention adherence, participants will complete a PA diary; and to collect data to assess study procedures, researchers in the three sites will keep records of recruitment parameters (e.g. number of participants screened, consenting) and completion of baseline and follow up measures.

Data to evaluate the other outcomes of the feasibility study will be collected as follows: proposed outcome measures for a future randomised controlled trial will be collected twice immediately before and immediately after the 12 week PA intervention. Each participant will meet with a researcher face to face to complete questionnaires (QoL and fatigue measures) hosted by Bristol Online Survey, which is an online service that allows researchers to develop, deploy and analyse an online survey. Participants with IBD only will have their blood taken by a nurse and the researcher will send the sample to the hospital laboratory for testing. Participants will be given an accelerometer that will be worn during waking hours for 7 consecutive days for 1 week. At the end of the 7-day period, participants will return the device to the research team by post.

#### Data analysis

Quantitative data analysis will be conducted in three steps. First, descriptive statistics will be used to describe demographic and clinical characteristics of the studied population stratified by eligible consenting and non-consenting participants, and screening, eligibility, consent and data completion rates and reasons for excluding patients reported as percentages. Second, intervention fidelity and intervention adherence continuous data (e.g. number of PA consultations, pedometer step count) will be presented as means and standard deviation and categorical data (type of consultation) as percentages. Third, assuming continuous data outcomes, differences pre- and post-intervention will be presented by the mean difference with the associated 95% confidence interval following *t* test analysis. This is because the focus of the results from this feasibility study will be on the estimates of treatment effects rather than statistical significant and hypothesis testing, which is the purpose of a full trial. Qualitative thematic analyses of audio-recorded interviews will be conducted using the Framework approach which is a rigorous method providing a structure within which qualitative data are organised and coded and themes identified [33].

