##### Assessing study procedures

Screening, eligibility, consent and data completion and loss to follow up rates and reasons for excluding patients will be presented as percentages. Recruitment rates will be measured as rate of invited participants who are eligible and consenting. Clinical information including diagnosis (e.g. cancer or IBD), surgery (e.g. open or laparoscopy), date of stoma surgery, disease staging, stoma type (e.g. permanent or temporary, ileostomy or colostomy) and demographic information (e.g. age, sex) will be collected to assess representativeness of participants. Suitability of measurement procedures will be evaluated based on completion rates and rates of missing data.

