#### Data management

The study includes three paper report forms: researchers in each site will complete a ‘recruitment form’ indicating if a patient is eligible to participate and screened patient clinical information (e.g. diagnosis); PA instructors will complete a ‘consultation form’ indicating duration and type of consultation; participants will complete a PA diary (e.g., prescribed activities). Data on paper report forms will be manually entered by a researcher into customised password encrypted spreadsheets in Microsoft Excel. A researcher will export data entered into Bristol Online Survey to the Statistical Package for the Social Sciences v19.0 for the purposes of analysis. All electronic data will be retained on a university password-protected server, and all paper records will be retained in a secure storage facility on university premises for a minimum of 10 years.

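### The planned comparison of consenting and non-consenting people does not separate recruitment routes, so its differences may partly reflect social-media recruitment as well as who agrees to take part

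*Protocol article*

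**What the plan says.** Representativeness of participants is part of objective 4 (Aim). Under Assessing study procedures, clinical and demographic information "will be collected to assess representativeness of participants". The Data analysis section states how it will be laid out: descriptive statistics for "demographic and clinical characteristics of the studied population stratified by eligible consenting and non-consenting participants". Recruitment route is not mentioned there.

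Participants arrive by three routes:

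- **Prospective:** "A stoma/colorectal nurse specialist will discuss the study with eligible patients and, if they are interested, will pass their contact details on" to the research team.
- **Retrospective:** the clinical team draws up a list, eligibility is re-assessed on it, and "The clinical team will send a letter of invitation to those that are eligible".
- **Social media:** an advertisement with brief eligibility criteria is circulated by stoma charities and the Patient Advisory Group. "This will allow anyone who is interested in taking part to see if they will be eligible and to contact the research team directly".

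The one stated comparison between routes concerns counts: "Three recruitment methods will be used and the number of patients recruited by each method will be compared". According to Data management, a site recruitment form holds eligibility and clinical information on screened patients. The recruitment target is 30 (Sample size).

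**The concern.** The two columns are not drawn from the same sources. In both clinic routes, eligible patients are identified before they decide, so those who decline or do not reply can be listed and described. On the social-media route a person becomes known only by making contact, and someone who scrolls past the advertisement leaves no record. That route therefore feeds the consenting column and contributes almost nothing to the other.

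If social-media volunteers differ from clinic patients in age, diagnosis or stoma type, the difference appears in the table and can be read as a difference between people who agree and people who refuse. The table could then suggest selection at consent that is absent, or hide selection that is present. The study is meant to inform recruitment to a full trial, and the two explanations call for different responses: one concerns how eligible patients are approached, the other which channels are used.

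**Working it through.** The target of 30 is set by judgement within a quoted range of 10 to 75. It comes from no formula, so there is no figure of the plan to reproduce. The check is of structure.

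**Definitions**

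- *w*: consenters minus non-consenters within the clinic routes, on some characteristic.
- *s*: share of the 30 consenters who came by social media.
- *g*: social-media consenters minus clinic-route consenters on the same characteristic.
- Assumption: all recorded non-consenters come from the clinic routes.

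The consenting column is a weighted mean of clinic and social-media recruits, so

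column difference = *w* + *s* × *g*.

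Only the 30 comes from the article. Every value of *w*, *s* and *g* below is an assumption.

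**Age, no selection at consent (*w* = 0), social-media recruits 15 years younger**

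- 5 of 30: 5/30 × 15 = 2.5 years
- 10 of 30: 10/30 × 15 = 5.0 years
- 15 of 30: 15/30 × 15 = 7.5 years

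Consenters look younger by these amounts.

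**A percentage characteristic, *w* = 0, *g* from 10 to 30 percentage points**

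- 0 of 30: 0 points
- 3 of 30: 1 to 3 points
- 6 of 30: 2 to 6 points
- 10 of 30: 3.3 to 10 points
- 15 of 30: 5 to 15 points
- 20 of 30: 6.7 to 20 points

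**Both effects present.** With *w* = 20 points, *g* = 30 points and 10 of 30 by social media, the difference is 20 + 10/30 × 30 = 30 points. Of these, 20 reflect consent and 10 reflect route.

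**Masking.** If 20 clinic recruits are on average 5 years older than non-consenters and 10 social-media recruits are 10 years younger than non-consenters, the column difference is (20 × 5 + 10 × (−10))/30 = 0. A true difference at consent disappears.

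**After the fix.** With the comparison restricted to the clinic routes, the *s* × *g* term drops out and the difference equals *w*.

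**The case against.** Several points can be made for the plan.

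- *The stated aim is representativeness of participants, and social-media recruits are participants.* If they make the sample younger than the eligible clinic population, the table ought to show it. This stands. A plain restriction to clinic patients would drop a legitimate question, so the total consenting column should be kept.
- *The article is condensed, and a breakdown by route may sit in a fuller plan.* The article does not rule one out, and route must be recorded for the comparison of methods. But it does state the stratification it will use, and the only route comparison it names is of numbers recruited. The point concerns that stated choice.
- *The table is descriptive, with no test or progression rule attached, and the full trial is to have an internal pilot at all sites.* This is correct and limits the consequence. The table will still be read as showing who agrees to take part.
- *The magnitudes are hypothetical.* They are. They show what could happen, and the route term is zero if either *s* or *g* is zero.
- *Splitting 30 people by route gives small cells.* This stands as a cost.

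A reader might go further and infer that social-media recruits have no comparable non-consenters at all, or that the column differences show route in place of consent. The text supports neither. A volunteer who makes contact, is found eligible and then declines is an eligible non-consenter. Clinic-route consenters and decliners remain comparable, and route adds to their difference without replacing it. Nor can one say which clinic route will supply most non-consenters, because no numbers by route are given.

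**Conclusion.** The point holds in a limited form. Followed as written, the comparison does not separate route from consent, and differences between its columns may partly reflect recruitment route. The bias is *s* × *g*: 5 years under the assumed 10 of 30 recruits and 15-year gap, and anywhere from 0 to 20 percentage points over the assumed ranges for a percentage characteristic. The article gives neither the social-media share nor the gap, so the actual size is unknown. The conclusion rests on non-responders to the advertisement going unrecorded, which follows from how that route works, and on few volunteers declining after making contact, which is an inference. The recruitment rate and the counts by route are outside this point. It is an inexpensive improvement to a descriptive table and invalidates no other part of the plan.

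**What to change.** In Data analysis:

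1. Keep a total consenting column, labelled as describing the representativeness of the enrolled sample.
2. Compare consenting with non-consenting people among patients identified through the clinical teams (prospective and retrospective), shown by route where numbers allow.
3. Show social-media participants in a separate descriptive column.

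The cost is a few extra table columns, one sentence of analysis text, and smaller cells in a sample of 30. If 10 came by social media, 20 clinic consenters would remain, divided over two routes, so the split by clinic route may have to give way to a pooled clinic comparison. No new data item is needed, because the planned comparison of recruitment methods already requires each participant's route.

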#### Ethical considerations

The research study has been approved by NHS North East Scotland (REC reference 17/NS/0065); IRAS project ID: 219548).

##### Consent

The ethical principles of ensuring freely given fully informed consent and the right to withdraw from research participation will apply. The right to anonymity when reporting findings will be emphasised.

##### Confidentiality

All participants will be informed that all of the information that they provide to the research team will remain confidential and will only be accessible to members of that team. Only personal information that is deemed vital for running this study will be obtained. Participants will be given a unique study identifier so that their name will be filtered out of any quantitative and qualitative datasets used for analysis.

##### Participant risk

The Association of Stoma Care Nurses (ASCN) UK recommends core muscle exercises to strengthen the abdominis in order to prevent parastomal hernia formation. However, ASCN also advise against lifting heavy objects since this may cause a parastomal hernia [34]. The American College of Sports Medicine roundtable on exercise guidelines for cancer survivors recommends for people who have a stoma that (a) physician-permission is obtained prior to participation in contact sports, (b) special consideration be put in place for swimming activities, (c) resistance programmes should begin with low resistance and slow progression and (d) flexibility programmes should pay particular attention to maintaining correct breathing patterns in order to avoid excessive intra-abdominal pressure [35]. We will ensure that all these recommendations are covered in the training programme for the instructors delivering the PA intervention in this feasibility study.

##### Safety reporting

The adverse event reporting procedures will follow those of NHS guidelines for research trials. Reporting of adverse effects will be included in participant diaries, and all participants will be advised and encouraged to report concerns to the research team, their stoma nurse and their PA instructor. All serious adverse events (SAE) and adverse events (AE) will be recorded. Any SAE or AE will be reported, regardless of considered link with intervention participation.

#### Data management

The study includes three paper report forms: researchers in each site will complete a ‘recruitment form’ indicating if a patient is eligible to participate and screened patient clinical information (e.g. diagnosis); PA instructors will complete a ‘consultation form’ indicating duration and type of consultation; participants will complete a PA diary (e.g., prescribed activities). Data on paper report forms will be manually entered by a researcher into customised password encrypted spreadsheets in Microsoft Excel. A researcher will export data entered into Bristol Online Survey to the Statistical Package for the Social Sciences v19.0 for the purposes of analysis. All electronic data will be retained on a university password-protected server, and all paper records will be retained in a secure storage facility on university premises for a minimum of 10 years.

## Discussion and dissemination

The findings from this feasibility study will be shared with interested parties and audiences on a national and international level. The intention of this feasibility study is to inform a full randomised control trial, and any outcomes and findings from this preliminary work will be disseminated on that basis.

Evidence suggests that feasibility studies do not guarantee success for the future trial and this is often due to poor recruitment [36]. There are a range of contextual factors influencing the success of a trial (e.g. delays in study starting due to research governance procedures, poor recruitment due to poor buy-in from the clinical team) and wide variation between sites, which is why in the future full randomised controlled trial there will be an internal pilot in all sites [36].

We will present the study findings to the Big Bowel Event which is organised by a UK research charity—Bowel and Cancer Research. Participants at the Big Bowel Event include patients with a stoma, clinicians and researchers. The audience will help the research team improve the intervention and study procedures in preparation for a randomised controlled trial. A limitation of this feasibility study is that we will not gather data about the acceptability of randomisation. We will, however, seek advice about what is the most acceptable comparator arm in a future full trial for example, wait-list control or usual care. A further limitation is that the feasibility study will not provide indication of the sample size needed for a future trial. We will seek advice at the Big Bowel Event regarding what would be a meaningful difference in outcomes between patients receiving a PA intervention and those who do not from a patient perspective and use their recommendation to estimate the sample size needed for a future trial. We will inform participants of the key findings if they agree to receive this information. We will share information at relevant conferences, and events of interest to the population involved. We will also provide a lay summary of the trial findings for public dissemination through charities, support groups and other interested parties.

Study recruitment began in December 2017 and is currently ongoing.

To the best of our knowledge, this is the first PA intervention study for patients with a stoma. There remains a limited evidence base about PA in the stoma population. Cross-sectional cohort studies highlight a trend toward inactivity after stoma formation surgery and a fear of exercise in general [14, 15]. However, there have been no PA intervention studies to date. This feasibility study represents crucial preliminary work leading to a multi-site, full randomised controlled trial.

## Data Availability

The datasets used and/or analysed during the current study are available from the corresponding author on reasonable request.

## Abbreviations

AE: Adverse event
CI: Confidence interval
FACIT: Functional Assessment of Chronic Illness Therapy
FACT-C: Functional Assessment of Cancer Therapy-Colorectal
IBD: Inflammatory bowel disease
MIDs: Minimal important differences
OR: Odds ratio
PA: Physical activity
QoL: Quality of life
SEA: Serious adverse event
SIBDQ: Short Inflammatory Bowel Disease Questionnaire
SPIRIT: Standard Protocol Items: Recommendations for Interventional Trials
